
It has not yet been examined whether cognitive-motor training including spatial orientation tasks is suitable to increase PA, enlarge LS mobility and to improve spatial orientation and, as a consequence, elicit changes in well-being and general cognitive-motor functioning in nursing home residents. Against this background, the overall goal of this multicentric RCT (PROfit) is to investigate the efficacy of three different intervention approaches on PA, LS mobility, and spatial orientation: The *PROfit basic* group will perform functional strength, balance, flexibility, and walking exercises at the same location, while the *PROfit plus* group relocates three times during the training. The *PROfit orientation* group receives navigation tasks in addition to the relocation during interventions. We hypothesize that all three intervention arms will generate slower decline or even improvements in residents’ PA, LS mobility, and spatial orientation compared to a wait-list control group. We assume that *PROfit plus* will be more effective than *PROfit basic* because of residents’ improved orientation due to the different training locations. Furthermore, we expect the *PROfit orientation* intervention to be most beneficial due to its additional focus on spatial orientation.

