##### Life-space mobility

The Nursing Home Life-Space Diameter (NHLSD) represents an external measure of LS mobility among nursing home residents [69]. This proxy-assessment will be administered to nursing staff and can be used to monitor changes or the effect of interventions on LS mobility [69]. The interrater (Pearson’s r = 0.951) and the intrarater (Pearson’s r = 0.922) reliability of the NHLSD is excellent [69]. The extent of LS mobility is measured by dividing the nursing home into four zones: (1) the resident’s private room, (2) the ward on which she/he resides, (3) the rest of the facility beyond the ward, (4) and the area outside of the facility [69]. Frequency of travels to each of the four zones is grouped into 0 = never, 1 = less than weekly, 2 = at least weekly, 3 = > 2 times a week, 4 = 1–3 times a day, and 5 = > 3 times a day; this score is then multiplied with 1 to 4 (congruent with the value of the zones, 1 to 4) and summed up. Independence of movement can be incorporated into the overall score by multiplying it with two in case of travel without human assistance.

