### Data collection, management, and analysis

#### Statistical analysis

Descriptive data will be reported as group mean values and standard deviations or medians and interquartile ranges depending on the type of outcome and their distribution. Analysis of baseline differences will be performed using a multivariate analysis of variance (MANOVA). Parametrical and normally distributed measures will be analyzed in separate 4 (group: PROfit basic, PROfit plus, PROfit orientation, wait-list control group) × 3 (test: baseline assessment, post-allocation, close-out-testing) analyses of variance (ANOVA) with repeated measures. If baseline differences are detected, baseline assessment values as well as age and sex discrepancies will be included as covariates in the statistical model. In the case of statistically significant interaction effects, Bonferroni-adjusted post-hoc tests (t-tests, Wilcoxon tests) will be performed to detect statistically significant differences in the groups between baseline- and post-allocation-testing. Kruskal-Wallis and Friedman tests instead of ANOVA will be used for non-parametrical variables and for data for which normal distribution could not be assumed. The effect size will be determined using Cohen’s *f* [95] which is indicative of the effectiveness of treatment and helps to assess whether a statistically significant difference is of practical concern. Cohen’s *f* values are classified as small (0 ≤ *f* ≤ 0.24), medium (0.25 ≤ *f* ≤ 0.39), or large (*f* ≥ 0.40). Additionally, PS_dep_ scores (probability of superiority for dependent samples) will be computed as an estimate of effect size in non-parametrical post-hoc tests [96]. The significance level will be set at *p* < 0.025.

Intention-to-treat analysis will be conducted. For this purpose, data of all participants will be processed in the groups into which they were randomly assigned, regardless of whether they received or adhered to the assigned intervention. The majority of participants are expected to take part in a minimum of 80% of the training sessions. An additional per-protocol analysis will be performed if a sufficient number of participants are lost to outcome assessment or insufficient participation in training sessions. Multiple Imputation will be used to handle missing data assuming that data are missing by chance.

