#### Sample size estimate / power calculations

The required sample size was calculated with G*Power (Version 3.1.9.2, Heinrich Heine University of Duesseldorf) [97]. The following input parameters were used to obtain small-sized test × group interaction effects: effect size (f = 0.15), type I error (α = 0.05), type II error (1-β = 0.95), number of groups (*n* = 4), number of measurements (*n* = 3), correlation between measurements (r = 0.60). Additionally, a dropout rate of 30% (i.e., 20% lost to follow-up; plus 10% deceased) was considered. Our analysis resulted in a total sample size of 513 participants (i.e., 171 per center with 42–43 participants allocated to each group).

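### The rank-test fallback for non-normal outcomes specifies no test of whether change differs between groups

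*Protocol article*

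**What the plan says.** Four parts of the protocol article bear on this.

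- **Hypothesis (Background).** Compared with wait-list, "all three intervention arms will generate slower decline or even improvements" in physical activity, life-space mobility and spatial orientation. This is a statement about differences in change.
- **Sample size (Sample size estimate / power calculations).** The calculation targets "small-sized test × group interaction effects: effect size (f = 0.15"), with four groups, three measurements and a correlation of 0.60.
- **Main analysis (Statistical analysis).** Normally distributed outcomes get 4 (group) by 3 (time) "analyses of variance (ANOVA) with repeated measures". Then: "In the case of statistically significant interaction effects, Bonferroni-adjusted post-hoc tests (t-tests, Wilcoxon tests) will be performed", to find "differences in the groups between baseline- and post-allocation-testing".
- **Fallback (same section).** "Kruskal-Wallis and Friedman tests instead of ANOVA will be used for non-parametrical variables and for data for which normal distribution could not be assumed". For non-parametric post-hoc tests the effect size is PS_dep, which is defined for dependent samples.

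The text does not say which variable Kruskal-Wallis is applied to, and it names no rank-based test of interaction.

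**The concern.** The fallback replaces a model that contains a group by time interaction with two one-way tests that do not. Kruskal-Wallis takes one value per person and compares groups. Friedman takes repeated values and compares time points, without regard to group. Whatever the pair shows, there is no interaction test to report.

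Two things follow. First, the effect the trial is powered for has no specified test in this branch. Second, the rule for going on to post-hoc tests cannot be applied: they open only "In the case of statistically significant interaction effects", and this branch produces none. The Wilcoxon tests in that same sentence are presumably meant for exactly these outcomes.

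The later steps do not fill the gap. The post-hoc comparison is worded as baseline against post-allocation within the groups, and PS_dep is also a within-group measure. Finding change in one group and none in another does not show that the two changes differ.

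Primary outcomes may be involved. The life-space score is built from ordinal frequency codes of 0 to 5; "this score is then multiplied with 1 to 4" according to zone, summed, and possibly doubled for independent travel. Step counts are often skewed. Whether either would take this branch depends on the data.

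**Working it through.** **1. The effect the trial is planned around.** Inputs from the sample size section: f = 0.15, alpha 0.05, power 0.95, k = 4 groups, m = 3 measurements, r = 0.60. Sphericity is assumed. For the within-between interaction:

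- lambda = f² × N × m / (1 − r) = 0.0225 × 128 × 3 / 0.40 = 21.6
- df1 = (4 − 1)(3 − 1) = 6; df2 = (128 − 4)(3 − 1) = 248
- Power = 0.952, so N = 128 in equal groups.

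Adding 30% gives 128 × 1.3 = 166.4, rounded up to 167 per centre, and 3 × 167 = 501. The stated total is 513 (171 per centre), so this is 12/513 = 2.3% short: close, not exact. It confirms that the planned total rests on the interaction. The point below does not depend on the exact N.

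**2. What the named tests respond to.** Simulation of skewed (log-normal) data with r = 0.60, 89 completers per group (513 × 0.7 / 4 = 89.8, rounded down), the plan's significance level of 0.025, and 1,500 replicates. The effects and baseline offsets, in SD units on the log scale, are assumptions chosen for illustration. Rejection rates:

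| Scenario | Friedman | Kruskal-Wallis at T2 | Kruskal-Wallis on T1–T2 change (log scale) |
|---|---|---|---|
| A. Same 0.4 SD decline in all groups, no interaction | 93–94% within a group, 100% pooled | 3% | 2.5% |
| B. No change; programme baselines +0.3, 0, −0.3 SD | 2–3% in a given group | 86% | 2.5% |
| C. Gains of 0.2, 0.3, 0.4 SD over wait-list, equal baselines | 93% (orientation), 2% (wait-list) | 50% | 64% |
| D. Gains as in C, cancelled by baseline offsets | 94% (orientation), 2% (wait-list) | 2% | 64% |

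Row A: Friedman rejects almost always although no programme works. Row B: Kruskal-Wallis at T2 rejects although nobody changed. Row C: with equal baselines, Kruskal-Wallis at T2 does detect the effect, with less power. Row D shows the mechanism only: it puts all three programmes below wait-list at baseline, which randomisation within homes makes unlikely at that size. With unequal groups (60, 60, 60 and 179), Kruskal-Wallis at T2 gives 67% in B, 58% in C and 2% in D, and the change-score test gives 2.5%, 71% and 71%.

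**3. Cost of ignoring baseline when baselines are balanced.** Linear-model illustration, unit variance at each time, r = 0.60:

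- T2 only: 1
- Change T1 to T2: 2(1 − 0.60) = 0.80
- T2 adjusted for baseline: 1 − 0.60² = 0.64

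T2 only therefore needs 1/0.80 = 1.25 times the participants of a change analysis, and 1/0.64 = 1.56 times those of a baseline-adjusted analysis.

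**The case against.** The strongest reply is that the article does not say what Kruskal-Wallis is run on. It is a k-sample test and works on change scores, and a condensed article may leave the input variable to the analysis plan. Part of this stands: the defect is that no test of differential change is specified, and one could be added easily. But the article does state the method choice, names two tests as the replacement, and keeps an interaction as the condition for the next step. A Friedman test beside Kruskal-Wallis also suggests separate tests of group and time.

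A reader might infer that the intervention effect goes wholly untested for these outcomes. The documents do not support that. Residents are randomised individually within each home after baseline, stratified by sex, age and cognitive performance, so a T2 comparison of programme with wait-list does estimate an intervention effect, less precisely. The weakness is greater between programmes, because the programme is assigned to the home and resident-level randomisation does not balance those groups. The plan's remedy for imbalance is covariates, which neither rank test can include.

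A reader might also quote the loss as 56%. That figure compares against baseline adjustment, which the plan uses only if baseline differences are detected. Against the T1 to T2 change contrast the figure is 25%. Both come from linear models and a planning value of r.

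Finally, the 4 by 3 interaction is not identical to the trial's question, because wait-list residents receive the programme after twelve weeks and T3 is no longer a controlled comparison. This is true, and is a reason to centre the replacement on T2.

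**Conclusion.** The point holds in this form: for non-normal or non-parametric outcomes the protocol replaces its group by time analysis with two tests that, as written, do not address whether change differs between groups. The rule for post-hoc testing cannot be applied in that branch, and the post-hoc tests and PS_dep are within-group.

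The size depends on the reading. If Kruskal-Wallis is run at T2 and baselines are balanced, the cost is efficiency: variance 1 against 0.80 or 0.64 at r = 0.60, and 50% against 64% rejection in the illustration. If programme groups differ at baseline, differences in level can be mistaken for effects; the 86% in row B rests on an assumed offset of ±0.3 SD. If Friedman results are read as evidence of effect, change common to all groups will be misread.

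How many outcomes are affected cannot be known in advance. The life-space score and step counts are plausible, not established. The protocol should be changed, but the point does not show that the hypothesis is untestable or that the parametric branch is affected.

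**What to change.** Replace the Kruskal-Wallis/Friedman branch with a between-group analysis of T2 adjusted for baseline, with the method fixed in advance for each outcome:

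- ordinal scores: rank-based ANCOVA or proportional-odds regression;
- skewed continuous outcomes: a log transform, or a robust or bootstrap variance.

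At minimum, state that Kruskal-Wallis is run on T1 to T2 change. In either case, let this test take the place of the interaction as the condition for post-hoc testing, and follow it with Bonferroni-adjusted contrasts between groups.

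The cost is analysis wording, slightly more programming, and a less familiar effect measure for ordinal outcomes. Data collection and sample size need not change.

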#### Primary outcomes

The following primary outcomes will be measured to evaluate the efficacy of the intervention programs (see Fig. 1):

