##### Physical activity

The “activPAL4™ micro” accelerometers (PAL Technologies Ltd., Glasgow, Scotland) will be worn to assess participants’ PA for a full 7 days. The main outcomes are the number of steps as well as the proportion of PA and sedentariness per day. The reliability was judged as good to excellent (inter-device reliability range = 0.79 to 0.99) and it is a valid measure for posture and motion during everyday PA [68].

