## Discussion

The overall goal of this multicentric RCT is to determine the effects of three different cognitive-motor training interventions on PA, LS, and spatial orientation in a sample of nursing home residents. We expect slower declines or even improvements in PA, LS mobility, and spatial orientation in participants of all three groups compared to wait-list controls. Regarding the secondary outcomes, we expect that physical functioning, cognitive functioning, and psychosocial well-being will be improved in all residents participating in one of the three intervention arms, when compared to the wait-list control group.

The interventions of the PROfit program combine components of exercise programs that have been proven to yield health benefits for nursing home residents [51, 93, 98, 99]. Especially the physical outcomes, e.g., walking capacity, muscle strength, and balance capacity have been shown to be improved by multicomponent interventions as conducted within the PROfit approach [91, 93, 100].

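### Eight instruments are primary and each is tested separately at p < 0.025 with no adjustment across them, so the chance of at least one false positive primary result is about 7% to 18%, not 2.5%

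*Protocol article*

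**What the plan says.** The Primary outcomes section opens with "The following primary outcomes will be measured to evaluate the efficacy of the intervention programs" and then lists, under five subheadings, eight instruments:

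- Mobility: iTUG.
- Physical activity: activPAL accelerometer.
- Life-space mobility: NHLSD.
- Spatial orientation: Perspective Taking Test, landmark tasks, pointing task and a 19-item self-report questionnaire on spatial strategies.
- Psychosocial well-being: SWLS.

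No instrument is named as decisive. For activPAL the text gives more than one main score: "The main outcomes are the number of steps as well as the proportion of PA and sedentariness per day".

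The Statistical analysis section fixes four things that matter here.

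- Each suitable measure gets its own group-by-test ANOVA: "Parametrical and normally distributed measures will be analyzed in separate 4" (group) × 3 (test).
- Other measures go to rank tests: "Kruskal-Wallis and Friedman tests instead of ANOVA will be used for non-parametrical variables".
- The one multiplicity adjustment comes after the omnibus test: "In the case of statistically significant interaction effects, Bonferroni-adjusted post-hoc tests (t-tests, Wilcoxon tests) will be performed".
- The one multivariate test concerns baseline only: "Analysis of baseline differences will be performed using a multivariate analysis of variance (MANOVA").

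On the level, the section says "The significance level will be set at" p < 0.025. The article does not say why.

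**The concern.** A per-test level of 2.5% limits the error of one test. With eight primary tests and nothing linking them, the chance that at least one crosses the threshold by luck is larger. Bonferroni on the post-hoc tests does not help at this step, because those tests are run only after an interaction has already been declared significant.

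At stake is how a mixed result is read. If one or two of the eight instruments show a significant interaction, the plan as written gives no basis for judging whether that exceeds what chance would produce across the primary set.

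**Working it through.** **Inputs from the article**

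- Number of primary instruments: 8 (Primary outcomes).
- Level per test: 0.025 (Statistical analysis).
- Planning inputs: f = 0.15, alpha = 0.05, power 0.95, 4 groups, 3 measurements, correlation 0.60 between measurements, 30% dropout, N = 513 or 171 per center (Sample size estimate).

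**Inputs assumed**

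- One omnibus test per instrument. This is the lowest count if every instrument is tested.
- Correlation between the outcomes' test contrasts. The article gives none, so a range of 0 to 0.9 is shown.

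**Step 1. Chance of at least one false positive, independent tests**

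1 − (1 − 0.025)^8 = 1 − 0.8167 = 18.3%. Whatever the dependence, the bound is 8 × 0.025 = 20.0%.

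**Step 2. The same with correlated tests**

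Eight chi-square tests on 6 degrees of freedom, (4 − 1) × (3 − 1), were simulated with equal correlation between the underlying contrasts.

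| Assumed correlation | At least one of 8 significant at 0.025 |
|---|---|
| 0 | 18.3% (exact) |
| 0.3 | about 17% |
| 0.5 | about 15% |
| 0.7 | about 11.5% |
| 0.9 | about 7% |

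**Step 3. A lenient count**

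One test for each of the three domains in the stated goal gives 1 − 0.975^3 = 7.3% if independent. That too is above both 2.5% and 5%.

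**Step 4. What a correction costs in power**

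The formula is the noncentral F for the within-between interaction: λ = f² × N × m / (1 − ρ), df1 = 6, df2 = (N − 4) × 2.

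First, the plan's own figure. At alpha 0.05 and power 0.95 the formula needs 127 completers, or 128 in four equal groups. Then 128 × 1.3 = 166.4, so 167 per center, and 3 × 167 = 501. This is within 3% of 171 per center and 513 in total. It comes close only when the calculation is read per center and multiplied by three.

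Next, the strictest case: Bonferroni over eight at an overall 0.025, so 0.025/8 = 0.003125 per test. Holm is never stricter than this.

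- Pooled: 513 × 0.7 = 359 completers, λ = 0.0225 × 359 × 3 / 0.4 = 60.6, power above 0.999.
- One center alone: 171 × 0.7 = 119 completers (rounded down), λ = 0.0225 × 119 × 3 / 0.4 = 20.1, power 0.70.

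With an overall alpha of 0.05, the per-test level is 0.05/8 = 0.00625. Power is again above 0.999 pooled, and 0.77 in one center. All these power figures ignore clustering by nursing home.

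**The case against.** The best defence has four parts.

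*The analysis plan will settle it.* A condensed article may leave a success rule to a separate plan, so the absence of such a rule is not held against it. But this article does not leave multiplicity open. It states the level, the separate tests and the place where Bonferroni applies. The point rests on those statements.

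*The 0.025 may already be a correction.* The article does not say so. If it were 0.05/2, it would cover two tests, not eight. It is also fair that the article never presents 0.025 as a familywise level; the contrast here is with a per-test level.

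*There is a second hurdle.* A claim about a specific difference must also pass the Bonferroni-adjusted post-hoc tests. This stands. The percentages above are for the omnibus result only, and the chance of a false specific claim is lower. The article does not define the family for that Bonferroni step, so reading it as within one outcome is an inference, though a natural one.

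*The 18% is the top of the range.* This stands too, and so the conclusion is given as a range.

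A reader might infer more than the document supports:

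- That there are 12 to 14 primary scores, with an error of 26% to 30%. The landmark task has three steps and the questionnaire three aspects, but the article does not say that each is tested. Only activPAL is stated to give several main outcomes, and its activity and sedentary proportions are likely to be strongly related.
- That the error is 34% or more, using 0.05. That alpha is only an input to the sample size calculation; no outcome is tested at it. The difference between the two alphas is a separate matter.
- That iTUG and SWLS do not belong among the outcomes because the Discussion gives the goal as to "determine the effects of three different cognitive-motor training interventions on PA, LS, and spatial orientation". The Outcome measures section names physical functioning, cognitive performance and psychosocial well-being as key domains, and both instruments fit there.
- That any isolated significant score would be reported as confirmed efficacy. The hypotheses concern physical activity, life-space and spatial orientation, and a lone SWLS result would not confirm them.

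**Conclusion.** The point holds in this form: eight unranked primary instruments, separate tests at 0.025, and no adjustment across them. If no intervention has any effect and each instrument gets one omnibus test, the chance of at least one false positive is 18.3% under independence and about 17% to 7% under assumed equal correlations of 0.3 to 0.9. Testing more than one activPAL score would add tests and could only raise these figures. The exact size depends on correlations that the article does not give, but every case examined exceeds both 2.5% and 5%. The issue should be corrected before analysis. It concerns how the primary results are interpreted, not what is collected.

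**What to change.** Name one score per primary instrument, including which activPAL score counts. Then apply Holm across the group × test interaction tests of all primary outcomes at one stated overall alpha. If a rank test replaces the ANOVA for a primary outcome, state which single p-value enters the procedure.

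Alternatively, the sponsor designates one primary score each for physical activity, life-space and spatial orientation, applies Holm across those three, and reports the other measures as secondary. Which scores to choose is the sponsor's decision. Either route keeps the planned 4 × 3 analysis and all data collection.

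The cost is some power per test. On the protocol's pooled assumptions the loss is negligible (above 0.999 with 359 completers at 0.025/8, ignoring clustering). If each center were analysed alone it would matter: about 0.70 at that level, against 0.89 at the unadjusted 0.025. Re-ranking outcomes would also need a registry update, and because it changes which registered outcomes are primary, it should be documented before the data are analysed.
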